- c) **MRI:** an MRI will be made at baseline to confirm the diagnosis of a meniscal tear. A radiologist, experienced in musculoskeletal radiology will judge the MRI. All MRI's will be evaluated by describing the quality of the meniscus based upon signal intensity, type of lesion; a traumatic or degenerative tear, and a horizontal or vertical tear. All other structures, such as the synovium, subchondral bone, ligaments, bursae and cartilage, will be judged as well.
- d) **X-ray:** an X-ray will be made at baseline and at 24 of follow up. A radiologist, experienced in musculoskeletal radiology will judge the X-rays. The joint space will be measured in all components corresponding to their narrowest part. We also plan a follow up moment at 5 years to identify the development or progression of OA.
- e) **IKDC:** The International Knee Documentation Committee developed the 'Subjective Knee Form' (2006). It was developed for knee-specific measurement of symptoms, function, and sports activities in patients with a variety of knee conditions, including ligament and meniscal injuries, articular cartilage lesions, and patellofemoral pain. The IKDC is a self-administered questionnaire with a total of 19 questions. Response options include dichotomous, 11-point numeric rating scales and 5-point Likert scales. All items, except item 10a, are converted to a score with a maximum of 100 indicating no restrictions in daily and sports activities and the absence of symptoms. The questionnaire takes approximately 5 minutes to complete. The IKDC 'Subjective Knee Form' has been validated for meniscal injuries by Crawford et al. 2007 (18) and was translated and validated in Dutch by Haverkamp D et al. in 2008 (21).
- f) The RAND-36 is a self-administered questionnaire and measures general health status. It consists of eight dimensions of health, including: Physical function, Role limitations due to Physical and Emotional problems, Bodily pain, General health, Vitality, Social function and Mental health. The RAND-36 has a total of 36 questions and the overall score varies between 0-100, where a higher score indicates a better function. Also, two aggregated scores can be calculated, based on the average scores of the Dutch population. These scores are the Physical and Mental component score and the averages have been set on 50. The RAND-36 takes approximately 10 minutes to complete.
- g) **EQ-5D5L - Quality of Life:** The generic effects on quality of life will be assessed with the Euroqol EQ-5D5L (22). This widely used quality-of-life instrument includes five dimensions

of health related quality of life, namely mobility, self-care, daily activities, pain/discomfort, and depression/anxiety. These five dimensions will be combined into a health state.

- h) *Costs and EQ-5D5L - Cost-utility*: To establish the costs, relevant cost items are identified, after which these costs are measured and values are placed on the cost items. These relevant cost items are: the total surgery time and the costs surgery versus the costs of physical therapy.  
Utility values will be calculated for the health states of the EQ-5D5L, using preferences elicited from a general Dutch population. The utility values will be used to compute quality-adjusted life-years (QALY-EQ-5L5D) by means of the area under the curve method.
- i) *TiC-P part II (Trimbos/iMTA questionnaire for Costs associated with psychiatric illness)* measures costs and consequences of productivity losses (indirect costs). Part II of the TiC-P is a shortened version of the Health and Labour questionnaire and is appropriate for the measurement of productivity losses in both physical and psychiatric conditions. It has 4 modules: absenteeism from paid work, production losses without absenteeism from paid work, unpaid work and nuisance in paid and unpaid work and contains of 11 questions (23). In this modified version of the TiC-P, prepared by prof. [name] of the VU University Amsterdam, we will also measure the use of healthcare services.
- j) *PSC (patient specific complaints)* is a patient reported questionnaire, in which patients report on specific activities and movements in which they experience symptoms. It contains of 28 normal daily activities and movements. The patient selects 3 activities or movements in which they experience symptoms and they prefer to improve in the next months. They are then asked to fill in a visual analogue scale (of 10 cm) in which report the amount of complaints they experience (24).
- k) *Tegner activity scale* is a numerical scale ranging from 0 to 10 (25). Each value indicates the ability to perform specific activities. An activity level of 10 corresponds to participation in competitive sports, including soccer, football, and rugby at the elite level; an activity level of 6 points corresponds to participation in recreational sports; and an activity level of 0 is assigned if a person is on sick leave or receiving a disability pension because of knee problems. An activity level of 5 to 10 is recorded only if the patient participates in recreational or competitive sports. The psychometric were tested by Briggs KK. et al. 2006 (26) and were found acceptable for patients with a meniscal injury of the knee.

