#### 8.1.2 Secondary Outcomes

1) Change in:

- General health, measured by RAND-36
- Quality of life, measured by EQ-5D5L
- Pain, measured with the VAS in rest and during weight bearing.
- Level of activity, measured by Tegner Activity Scale (TAS)
- Patient specific complaints measured by the PSC (patient specific complaints) Questionnaire
- Treatment group; number of patients initially treated conservatively, treated secondarily by APM.

We will use the EQ-5D5L to measure Quality Adjusted Life Years (QALY).

2) Productivity losses and the use of healthcare services, measured by a modified version of the Trimbos/iMTA questionnaire for Costs associated with Psychiatric Illness (TiC-P).

3) Relation between a participants expectation of treatment and their satisfaction.

4) PE, consisting of performance on physical tests (squatting with duckwalk, Thessaly test, McMurray), the range of motion, joint line tenderness and the existence of joint effusion in the knee.

5) Adverse events including:

- Minor: prolonged synovial fluid leakage from arthroscopy portals and bleeding.
- Moderate: surgical site infection, vascular and neurological damage
- Severe: septic arthritis, cardiac events, pulmonary embolism and death.

Surgical instrument malfunction will be recorded, as well as reoperations including knee arthroplasties and re-hospitalization.

6) We plan a follow up moment at 60 months to see the progression of osteoarthritis, measured with the Kellgren Lawrence Grading Scale for Osteoarthritis.

Hypotheses:

1) We assume equal improvement of physical function in both groups (a difference of < 8.8 points on IKDC 'Subjective Knee Form'). This would question the role of arthroscopic surgery in treatment of symptomatic, non-obstructive meniscal injuries in patients over 45 years old.

2) We assume with an equal improvement of function in both groups, that an initial conservative approach for this condition in older patients is much more cost-effective than APM as standard therapy.

3) We assume a lower baseline value of participants compared to the average score of the Dutch population and an equal improvement of general health in both groups (RAND-36).

4) We assume equal improvement of quality in life, measured in QALY's.

5) We assume equal improvement of pain, measured with the VAS score.

6) We assume equal improvement of activity level (Tegner Activity Score).

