7) We assume equal improvement of complaints in activities and movements found most important by patients (patient specific complaints).

8) We expect a greater reduction of joint line tenderness in the arthroscopic partial meniscectomy group shortly after therapy, compared to the physical therapy group, since part of the damaged meniscus is released. However, we expect no difference in joint line tenderness on the long term. We expect a faster reduction of joint effusion after treatment in the physical therapy group. However, we do not expect a difference between both groups after 24 months. We do not expect a significant improvement of ROM after treatment in both groups.

9) We estimate that 2/3 of surgeries can be prevented (as stated by Herrlin SV et al. (6), and therefore expect 1/3 of patients who will undergo delayed arthroscopic meniscectomy after completion of physical therapy. The possible cost reduction of this effect will be calculated in the economic analysis.

10) Patients in the physical therapy group will leave work for at least 16 sessions of 30 minutes each week, representing one working day, with the addition of travelling time. Patient in the surgery group are expected to be absent from work for one working day, the day of surgery. We therefore expect surgery to lead to more productivity losses.

11) We expect squatting to have the greatest predictive value of the different meniscal tests for detecting meniscal injuries.

12) We expect a faster development or progression of osteoarthritis after arthroscopic partial meniscectomy compared to physical therapy.

13) We expect adverse events to occur more frequently in the arthroscopic partial meniscectomy group. Patients who are subjected to delayed surgery after physical therapy has failed, remain in the physical therapy group. Therefore, we do expect adverse events to occur in the physical therapy group. Since the number in the arthroscopic partial meniscectomy group are to be expected to outnumber the number of patients with delayed surgery, we expect more adverse events in the arthroscopic partial meniscectomy group.

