## 8.2 Randomization, blinding and treatment allocation

We will include 320 patients between 45 and 70 years with MRI-confirmed symptomatic, non-obstructive meniscal tears. Randomization will be performed in a 1:1 ratio by a computerized software program (TENALEA Clinical Trial Data Management System) using random blocks with maximum block size 6, stratified for center and age group.

- a. Open study (no blinding)
- b. Number of randomization arms : 2
- c. Specification of the arms : APM vs PT
- d. Weight of the arms : 1:1
  - Type of randomization : Random block, max block size 6
- e. Strata and categories:
  - Age : (45-57) and (57-70)
  - Centers : a maximum of 10
- f. No deletion or replacement of participants (unless false randomization due to clear technical issues)

At time of presentation at the outpatient department, people suspected for a meniscal injury will be informed about the study with an information letter. When they return to the outpatient department for the results of the MRI, they will be asked for participation in the study. After informed consent is signed, the local physician/surgeon contacts the randomization website and submits a patient's details and treatment center to the online TENALEA data management program and receives treatment allocation when submitting this information to the website. All data management will be recorded online, unless patients are unable or unwilling to complete the questionnaires online.

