## 10. STATISTICAL ANALYSIS

Data-analysis and presentation:

To investigate the effect of surgery, we will use generalized estimating equations (GEE) for longitudinal analysis in SPSS 18 on an intention-to-treat and per-protocol basis, as well as sub-group analysis of the cross-over patients. This method takes into account the dependency of observations within a patient, and the fact that not all patients may be assessed at each time point (missing data). In the primary GEE model, the outcome variable studied (e.g. physical function on the IKDC) will be analyzed as a dependent variable, using treatment allocation (1, intervention; 0, control) and time as a key independent variables. In the secondary GEE model, the outcome variables studied (e.g. general health on the RAND36, quality of life on the EQ5D-5L, level of activity on the TAS, knee pain on the question 10 of IKDC, the correlation between a patient's expectation and satisfaction, productivity losses on TiC-P, muscle strength, range of motion, squatting and adverse events) will be analyzed in a similar way. To evaluate whether the two groups differed in change over time the interaction term of group and time (group X time) will be assessed. Time will be included as a dummy variable (reference = baseline T0), and four interaction terms will be analyzed (T1Xgroup; T2x group; T3x group, T4x group). All models will be corrected for center of inclusion and age group. In additional analysis, we will investigate the possible confounding effect (defined as more than 10% change in the parameter estimate for groupXtime) of 5 variables (body mass index, gender, profession, ASA-classification, the affected meniscus, the type of tear and the stadium of OA according to the Kellgren Lawrence Grading Scale for Osteoarthritis).

At the following time points following the treatment (T2, T3, T5 and T7) we will describe the incidence of revisions (intervention group) or treatment failures (=delayed APM, control group) using descriptives. After two years (T7) we will compare the incidence of development or progression of OA between groups using a chi-squared test (or Fisher's Exact as appropriate). For all analysis, a two-tailed value of  $p < 0.05$  is considered to be significant.

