#### Cost analysis:

The total number of patients aged 45 to 70 years who were diagnosed with symptomatic, non-obstructive, MRI confirmed meniscal tears will be estimated based on Dutch incidence and prevalence rates. Resource utilization is calculated by multiplying the number of eligible patients with the resource utilization rates obtained from the cost-effectiveness analysis.

Different prices will be used to value resource use depending on the perspective of the analysis: Dutch standard costs for the societal perspective, actual NZA tariffs for the government perspective, and average tariffs NZA for the insurer perspective.

Both resource use and annual costs will be presented over a 5 year period for all perspectives. Aggregated and disaggregated total costs per year will be presented for the different perspectives and scenarios. For the long term analysis total costs over the whole time horizon will be estimated.

Data analysts will be blinded to the type of treatment by numerical coding of the performed intervention. After finalizing data analysis this code will be broken for publication purposes.

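### Masked reading of the X-rays for osteoarthritis progression is not specified in a trial declared to have no blinding

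*Protocol*

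**What the plan says.** Protocol Section 8.2 lists the randomisation settings. Its first item is "Open study (no blinding", with no exception for outcome assessors.

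Section 8.3 d) plans X-rays at baseline and 24 months, with a further follow-up at 5 years. On reading it says "A radiologist, experienced in musculoskeletal radiology will judge the X-rays" and "The joint space will be measured in all components corresponding to their narrowest part". It does not mention allocation, treatment received or clinical information. Section 8.1.2 adds "progression of osteoarthritis, measured with the Kellgren Lawrence Grading Scale for Osteoarthritis", again without a word on masking.

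Three other statements bear on this:

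- **Hypothesis 12, Section 8.1.2:** "We expect a faster development or progression of osteoarthritis after arthroscopic partial meniscectomy compared to physical therapy".
- **Section 10, at two years:** "we will compare the incidence of development or progression of OA between groups using a chi-squared test", or Fisher's exact test. The section sets a two-tailed 0.05 level for all analyses.
- **Section 10, end of the Budget Impact Analysis:** "Data analysts will be blinded to the type of treatment by numerical coding of the performed intervention". This is the only masking in the protocol.

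**The concern.** Grading a knee film is partly judgement. In Appendix C, grade 1 rests on narrowing that is in doubt and lipping that is only possible, and grade 3 includes a deformity that need only be possible. One borderline call can decide whether a knee counts as progressed. A reader who knows that the knee had surgery, in a project whose protocol expects surgery to do harm, may resolve such calls differently in the two arms.

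Masking the data analysts cannot undo this, because the grades are fixed before analysts receive them.

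Patients and treating clinicians cannot readily be masked in a comparison of surgery with physical therapy, and the primary outcome is self-reported. Film reading is a step where allocation-related observer bias can be prevented. At stake is the credibility of the between-arm osteoarthritis result at 24 months and again at 5 years. Section 10 also plans a long-term budget estimate that quantifies an expected decrease in osteoarthritis progression.

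**Working it through.** **What the text settles.** Side by side, Section 8.2 declares no blinding, Section 8.3 d) names the reader and is silent on masking, and Section 10 masks the analysts only. Sections 5 and 6.3, which also mention the Kellgren-Lawrence scale, add nothing on masking. So masked reading is not specified. Nor does any passage say that the reader is given the allocation.

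**The plan's own figure.** There is none for osteoarthritis. The 160 per group in Section 6.4 is for the IKDC: 2 × (1.96 + 1.2816)² × 18² / 8² = 106.4, so 107. Then 107 / (0.90 × 0.75) = 158.5, so 159, close to the stated 160. It is used here only for the number of films.

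**Inputs for the illustration.**

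- Films per arm at 24 months: 160 × 0.90 = 144 (Section 6.4, 10% loss to follow-up).
- Test: two-sided, 0.05 (Section 10).
- Share of the PT arm with delayed APM, f: 25% (Section 6.4) or 1/3 (hypothesis 9). Section 7 keeps these patients in the PT group.
- True progression p, equal in both arms: assumed 20%, varied from 10% to 40%.
- Share x of stable operated knees upgraded to progressed: assumed 5% or 10%.

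**Formulas.** Observed progression in the APM arm is q1 = p + (1 − p)x. In the PT arm it is q0 = p if the reader acts on the arm, and q0 = p + (1 − p)xf if the reader acts on surgery. With d = q1 − q0 and q̄ = (q0 + q1)/2:

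- s0 = √(2q̄(1 − q̄)/144)
- s1 = √((q0(1 − q0) + q1(1 − q1))/144)
- rejection probability = P(Z > (1.96·s0 − d)/s1) + P(Z < (−1.96·s0 − d)/s1)

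**Worked case: p = 20%, x = 5%, reader acts on the arm.** q0 = 0.20, q1 = 0.20 + 0.80 × 0.05 = 0.24, d = 0.04, s0 = s1 = 0.0488 to three figures. The critical difference is 1.96 × 0.0488 = 0.0957. The upper tail is P(Z > 1.14) = 0.127 and the lower tail is 0.003, in total 0.129. Nearly all the false positives point against APM.

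**All cases at p = 20%.**

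| x | Reader acts on | q0 | q1 | d | Rejection probability |
|---|---|---|---|---|---|
| 0 | nothing | 0.200 | 0.200 | 0 | 5.0% |
| 5% | arm | 0.200 | 0.240 | 0.040 | 12.9% |
| 5% | surgery, f = 25% | 0.210 | 0.240 | 0.030 | 9.3% |
| 5% | surgery, f = 1/3 | 0.213 | 0.240 | 0.027 | 8.4% |
| 10% | arm | 0.200 | 0.280 | 0.080 | 35.5% |
| 10% | surgery, f = 25% | 0.220 | 0.280 | 0.060 | 21.7% |
| 10% | surgery, f = 1/3 | 0.227 | 0.280 | 0.053 | 18.0% |

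Exact enumeration of the chi-squared test gives the same values within half a percentage point (13.1% and 35.9% for the two arm-driven rows).

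**Range for p from 10% to 40%.** If the reader acts on the arm, the rejection probability runs from about 21% down to 8% (x = 5%) and from 58% down to 18% (x = 10%). If the reader acts on surgery, over both values of f, it runs from about 14% down to 6% and from 35% down to 10%.

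**The case against.** A reader might infer that the protocol has chosen unmasked film reading. The documents do not support that. The no-blinding entry sits in a list of randomisation settings, and the later masking of analysts shows that it was not meant to cover every role. Section 8.3 d) is silent; it does not say that the reader knows the arm.

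A reader might also infer that the osteoarthritis result will be biased against APM. That goes too far as well. Hypothesis 12 is the investigators' expectation, and nothing shows that the radiologists share it. Joint space measured at its narrowest part leaves less discretion than the Kellgren-Lawrence wording. The text supports only that the result can be biased.

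On size, the upgrade rates and the progression rate have no source in the documents. If the reader reacts to surgical history, the PT patients with delayed APM are upgraded too, which dilutes the bias. This stands, and the working shows both cases.

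On weight, osteoarthritis is a secondary outcome, and the budget analysis varies the arthroplasty reduction in a sensitivity analysis. Film reading is also not the only observer-assessed outcome, since the 3-month physical examination is another. All of this limits the point, but none of it removes the gap.

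The statistical analysis plan, which is not at hand, would not close the gap. Who reads the films, and with what information, is a study procedure, and an analysis plan cannot mask a reading already made.

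**Conclusion.** The point holds as a gap with a cheap remedy. The protocol declares the trial open, does not specify masked X-ray reading, expects a difference in one direction, and tests that difference formally. The only masking stated comes too late to protect the grades.

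The size is illustrative. At 20% true progression and 144 films per arm, the false-positive rate rises from 5% to between about 8% and 13% with 5% of stable operated knees upgraded, and to between about 18% and 36% with 10% upgraded. The upper figure in each pair needs a reader who acts on the randomised arm alone. The lower figures need a reader who acts on surgery, with all delayed APM done before the 24-month film.

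The IKDC comparison, the sample size and the non-inferiority conclusion are untouched. The change is worth making, but the primary result does not depend on it.

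**What to change.** In Section 8.3 d), state that the radiologists already planned will grade the 24 and 60 month films, against the baseline film, from images that carry only the study number, without access to allocation, surgical history or clinical notes.

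In Section 8.2, limit the no-blinding statement to patients and treating clinicians, so that it no longer appears to cover film readers and data analysts.

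No extra reader, film or visit is needed, and no treatment changes. The change is not free, because each centre must remove identifiers and clinical information from its films and handle the exported images.

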#### 8.4 Study scheme

At the initial presentation, an MRI-scan will be obtained when a meniscal injury is suspected. Patient will also be informed about the trial and will be given a patient information latter. In case a meniscal injury is diagnosed, patients will be asked to participate in the trial.

After informed consent is signed at the outpatient department (t0), patients will be entered in an online randomization program and are assigned to either arthroscopic partial meniscectomy (within 4 weeks) or physical therapy. They are asked to complete CRF t0. 3 months after treatment, they will return to the outpatient department to check for function. A physical examination is performed, and they will be asked to complete CRF t2. At both 6 (t3), and 12 (t4) months they will not visit the outpatient department and they are online asked to complete the corresponding CRF. For an overview of assessments, see figure 1 or table 1. At 24 months they will be asked to visit the outpatient department for an X-ray and to complete CRF t5 as endpoint of the study.

In case patients in the physical therapy group don't show any improvement, they will be held the choice of delayed arthroscopic partial meniscectomy. This will be determined by agreement between participant and surgeon. Each CRF is calculated to take no more than 30 minutes.

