### FOLLOW-UP:

Patients will visit the outpatient department for physical examination (3 months) and X-rays (24 months). All measurement outcomes will be obtained at baseline, 3, 6, 9, 12, 18 and 24 months, online or by hardcopy if preferable. Patients will be examined by a well experienced clinician at each site. The anticipated enrolment period will be approximately one year with follow up.

We also plan to perform another long-term outcome measurement after 5 years.

Endpoint: the first results of the study will be evaluated after 1 year of follow up. The endpoint for the primary outcome of the study will be after 2 years of follow up. However, we plan a follow up moment at 60 months to see the progression of osteoarthritis, measured with the Kellgren Lawrence Grading Scale for Osteoarthritis.

Sample size calculation:

Sample size is based on a power of 90%, an alpha of 0.05, a standard deviation of 18 points and a non-inferiority threshold of 8 points on the IKDC 'Subjective Knee Form'.

We calculated that with 10% loss to follow-up after 24 months and 25% delayed APM in PT group, 160 patients are needed per group in this equivalence type RCT. This means a total of 320 patients will be included. Sample size is calculated for the intention-to-treat analysis.

Assigning patients to treatment groups:

After signing and dating the informed consent form, patients will be randomized. This will be done in a web-based system, using the ALEA software, stratified for each site and for 2 age subgroups:

Subgroup 1: 45-57 years of age

Subgroup 2: 58-70 years of age

Patients who are excluded from the study will get treatment at the discretion of the surgeon. Patients who prefer not to participate will be asked for their reasons. These reasons will be recorded.

Data Management:

Database management will be done using a web-based system.

Safety: the occurrence of adverse events and subsequent knee surgeries will be queried and recorded at follow-up visits.

[figure not shown]**Figure 1: Study Flowchart**

\* Total follow up time for primary outcome in delayed APM group remains 24 months

CRF s\* = surgery / CRF c\*=conservative, CRF d\*=delayed

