#### **Nature and extent of the burden and risks associated with participation, benefit and group relatedness:**

At baseline, when a meniscal tear is suspected at presentation, an MRI-scan will be obtained. This is not seen as an extra burden for participants, since an MRI which has a high sensitivity and specificity normally is usually made to avoid unnecessary diagnostic arthroscopies as stated in the guideline for arthroscopy of the knee, 2010 (NOV) (1).

All patients approached and willing to participate in the trial will be randomized when all inclusion criteria are met when they return to the outpatient department for the results of the MRI.

Participants will be randomized into the surgical group or the conservative group and are followed at 3, 6, 9, 12, 18 and 24 months.

The risks associated with participation in the trial include the general risks for surgery, e.g. infection, bleeding, postoperative numbness, paralysis, pain, persistence of symptoms when randomized into the surgical group. In the conservative group, no specific risks are known to occur. Since surgery is current standard treatment, there are no additional risks for participation in this trial.

All patients will return to the outpatient department after 3 and 24 months. This will be for PE (3 months) and X-rays (24 months).

We plan a follow up moment at 60 months to see the progression of osteoarthritis, measured with the Kellgren Lawrence Grading Scale for Osteoarthritis.

The burden of the extra X-ray will be negligible, especially when focused on the potential outcome of the trial, which could lead to a significant reduction of unnecessary surgeries.

All questionnaires will be obtained digitally and can be completed at home. If preferred, a hardcopy can be sent to these participants.

Completion of the questionnaires will take approximately 30 minutes. The questionnaires at 9 and 18 months consist only of the EQ-5D-5L and TiC-P and will take only 5 minutes to complete.

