**Table 1: measurement moments**

| Baseline (t0) | 1-2 months
(t1) | 3 months
(t2) | 6 months
(t3) | 9 months
(t4) | 12 months
(t5) | 18 months
(t6) | 24 months
(t7) |
|---------------|--------------------|------------------|------------------|------------------|-------------------|-------------------|-------------------|
| CRF-1  |                    | CRF-2     | CRF-3     | CRF-4     | CRF-5      | CRF-6      | CRF-6      |
| Visit 1       | Treatment          | Visit 2          | No visit         | No visit         | No visit          | No visit          | visit 3           |
| Randomization | APM or PT          |                  |                  |                  |                   |                   |                   |
| IKDC          |                    | IKDC             | IKDC             |                  | IKDC              |                   | IKDC              |
| RAND-36       |                    | RAND-36          | RAND-36          |                  | RAND-36           |                   | RAND-36           |
| EQ-5F5L       |                    | EQ-5D5L          | EQ-5D5L          | EQ-5D5L          | EQ-5D5L           | EQ-5D5L           | EQ-5D5L           |
| VAS           |                    | VAS              | VAS              |                  | VAS               |                   | VAS               |
| TAS           |                    | TAS              | TAS              |                  | TAS               |                   | TAS               |
| PSC           |                    | PSC              | PSC              |                  | PSC               |                   | PSC               |
| TiC-P         |                    | TiC-P            | TiC-P            | TiC-P            | TiC-P             | TiC-P             | TiC-P             |
| PSC           |                    | PSC              | PSC              |                  | PSC               |                   | PSC               |
| PE            |                    | PE               |                  |                  |                   |                   |                   |
| X-ray         |                    |                  |                  |                  |                   |                   | X-ray             |

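### The protocol does not secure the baseline IKDC before allocation is disclosed, so in this open trial an allocation-driven difference in baseline reporting can enter the primary contrast one-for-one, in either direction

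*Protocol*

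**What the plan says.** Section 8.4 (Study scheme) gives the only step-by-step account of the first visit. It begins: "After informed consent is signed at the outpatient department (t0), patients will be entered in an online randomization program and are assigned to either" of the two arms. The next step is the baseline form, since patients are "assigned to either arthroscopic partial meniscectomy (within 4 weeks) or physical therapy. They are asked to complete CRF t0".

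Other sections fit this order:

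- Section 5, under the paragraph on assigning patients: "After signing and dating the informed consent form, patients will be randomized".
- Section 8.2: after consent, the local physician enters the patient on the website and "receives treatment allocation when submitting this information to the website". The same section declares the study open.
- Section 6.3, on burden: "All questionnaires will be obtained digitally and can be completed at home". No exception is made for the baseline set.

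Table 1 places randomization, the IKDC, the EQ-5D-5L and the expectation item together in the t0 column, without an order within the visit. Sections 5 and 8.1.1 define the primary outcome as change in IKDC from baseline to 2 years and describe the IKDC as self-administered. Section 10 fits a GEE with baseline T0 as the reference level of time and assesses the group-by-time interaction. Among the secondary outcomes, Section 8.1.2 lists: "Relation between a participants expectation of treatment and their satisfaction".

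**The concern.** Randomization makes the arms comparable on anything measured before allocation is known. It gives no such protection to a self-reported score recorded afterwards. A patient who has just learned that they will have surgery, or that they will have physical therapy (PT) instead of what the protocol calls standard treatment, may rate the same knee differently. The primary outcome subtracts that rating, so a difference between arms in baseline reporting becomes a difference in measured change.

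The consequence depends on direction. If PT patients report a lower baseline than they would have before allocation, their improvement is overstated and non-inferiority is declared too easily. If they report a higher baseline, or surgical patients a lower one, PT looks worse and the trial loses power. In both cases no pre-allocation baseline exists for those patients, and no later analysis can recover one.

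**Working it through.** **Inputs.** SD 18, margin 8 IKDC points, power 90%, 10% loss, 25% delayed surgery in the PT arm, 160 per group (Section 6.4). Two-tailed 0.05 (Section 10), taken as one-sided 0.025 for non-inferiority. 1:1 allocation (Section 8.2).

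**Reproducing the plan's own figure.** n = 2 × [18 × (1.960 + 1.282) / 8]² ≈ 106.4, so 107 per arm. Inflated for both allowances: 107 / (0.90 × 0.75) = 158.5, so 159, against 160 stated. The inputs are therefore read as the plan used them.

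**How a baseline shift enters.** The contrast is D = (PT at 24 months − PT at baseline) − (APM at 24 months − APM at baseline). If knowing the arm lowers the reported PT baseline by b points relative to APM, D rises by exactly b. If it raises it by b, D falls by exactly b. The same holds for the group-by-time term at 24 months, because T0 is its reference.

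**Assumptions for the illustration.** The documents give no value for b, so 1 and 2 points are chosen in each direction. SD 18 is treated as the SD of change, which Section 6.4 does not specify.

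**Standard error.** SE = 18 × √(2/n).
- 144 per arm (160 less 10% loss): SE = 2.12.
- 108 per arm (160 × 0.90 × 0.75, after both planned allowances): SE = 2.45.

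**Shift towards PT, true deficit equal to the margin (8 points).** False non-inferiority rate = Φ(b/SE − 1.96).

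| b | 144 per arm | 108 per arm |
|---|---|---|
| 0 | 2.5% | 2.5% |
| 1 | 6.8% | 6.0% |
| 2 | 15.5% | 12.6% |

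**Shift against PT, true difference zero.** Power = Φ((8 − b)/SE − 1.96).

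| b | 144 per arm | 108 per arm |
|---|---|---|
| 0 | 96.5% | 90.4% |
| 1 | 91.0% | 81.5% |
| 2 | 80.7% | 68.8% |

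The 90.4% at 108 per arm and b = 0 agrees with the planned 90%.

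**The case against.** The strongest reply is that the order is read from loose narrative. Section 8.4 puts assignment and CRF t0 in consecutive sentences without saying then or afterwards. The same paragraph labels 12 and 24 months t4 and t5, where Table 1 has t5 and t7. Table 1 gives no order within the visit, and Figure 1 is not available here. Sites may in practice collect the form first. This stands to the extent that one cannot say baseline forms are in fact completed after allocation. It does not remove the point: the only order described is the unprotected one, and nothing elsewhere rules it out.

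The statement on home completion concerns questionnaires in general. It permits a baseline form to be completed after the visit but does not show that this is intended.

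The 24-month IKDC remains unblinded self-report whatever is done at baseline. That is true, so the fix removes one part of open-label reporting bias and not all of it.

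Three stronger readings are tempting and not supported:

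- *The EQ-5D-5L has the same problem.* QALYs are computed as area under the curve (Section 8.3), not as change from baseline. With the first interval 0 to 3 months, the baseline value has trapezoid weight 0.25/2 = 0.125 years out of 2, about 6%. A lower PT baseline would slightly reduce PT QALYs, the opposite of its effect on IKDC change.
- *Baseline becomes unsafe as an adjustment covariate.* Section 10 adjusts for center and age group, and its list of possible confounders contains no baseline score.
- *The expectation item is invalid.* Asking what a patient expects of a treatment they know they will receive is a legitimate question. Its meaning does depend on whether the arm is known, so the protocol should say which is intended.

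**Conclusion.** The point holds as a gap in procedure: the protocol describes allocation before the baseline form and nowhere secures the reverse. Because the primary outcome is change from a self-reported baseline in an open trial, a differential shift in baseline reporting passes in full into the primary contrast.

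That pass-through follows from the stated outcome and model. The size and direction of any shift do not follow from the documents. The error rates and powers above are scenarios showing that shifts well below the 8-point margin would matter. A reader might infer that the plan is biased in favour of PT; the documents do not support that, since the shift could equally go against PT and cost power instead. What is supported is that allocation can bias the primary effect and that the protocol does nothing to prevent it at baseline.

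**What to change.** State in Sections 8.2 and 8.4 that CRF t0 is completed after consent and before the randomization website is accessed, and make a completed CRF t0 a condition for randomization. Say there too whether the expectation item is meant to be answered before or after the arm is known.

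The cost is about 30 minutes at the consent visit, the completion time given in Sections 6.3 and 8.4, or a short delay to randomization for patients who prefer to complete the form at home. No measurement is added, and the sample size stays at 160 per group.
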